### **Data Collection**

The UVA Multi-Schema Information Capture (MuSIC) database will be used by all sites for electronic data entry. Delivery room data will be written on the DR script by the VFF or Neonatology provider during or immediately following the intervention. Some of the data may be available in the electronic medical record and/or on audiotape for validation. The data will be entered into the MuSIC database by the clinical research coordinator (CRC) after delivery.

With the exception of some of the study intervention delivery data, all data required for this study should be documented in the infant's medical record as part of routine care.

All study data should be entered into MuSIC by each site based on the data entry guidelines specified in the MOP.

## 6 OUTCOME MEASURES

All outcomes measures will be part of routine care and recorded in the medical record, with the exception of outside expert readings of HUS at 7-10 days and last HUS at birth hospital prior to 36 weeks.

### **Specification of the Appropriate Outcome Measures**

Multiple head ultrasounds are performed as routine care for all EPT infants. At each site, HUS will be performed 7-10 days after birth (nearly all IVH occurs before this time), and this will be used for primary outcome assessment. Failure to obtain a 7-10 day HUS will be considered as a protocol deviation, and the subsequent HUS accepted for the purposes of determining the primary outcome as discussed in section 7 on statistics.

The HUS performed at the birth hospital closest to the 36 week PMA follow-up time point will be used for the secondary HUS outcome assessment. The primary reason for the late HUS is to evaluate for cystic periventricular leukomalacia, which is usually not present on the 7-10 day HUS but can be associated with adverse perinatal and birth events and is associated with adverse long-term neurologic outcomes. The final HUS is also important for assessing post-hemorrhagic hydrocephalus, which evolves over time and is associated with severe (Grade III-IV) IVH and adverse long-term neurologic outcomes. If a center performs brain MRI rather than HUS near 36 weeks PMA, this will be used for secondary outcomes assessment.

**For clinical care and for adverse event reporting**, all HUS's will be read per standard of care by board-certified pediatric radiologists trained in neonatal HUS interpretation at each study site. These reports will not be used for primary or secondary study outcomes assessment.

**For study endpoints**, an independent radiologist at non-study institutions (blinded to study assignment) will independently read the 7-10 day and the final 36 week PMA HUS on each study infant. These readings will be performed in batch at intervals to be determined by the statistical analysis plan and DSMC requirements. Any HUS with discrepant findings between the local and the independent radiologist that would impact primary outcome assessment will be evaluated by another independent radiologist.

Quality review of each HUS will be performed by board-certified pediatric radiologists trained in neonatal HUS interpretation at each study site. If

studies are judged to be of poor quality for standard interpretation, they will be repeated as part of routine clinical care.

Detailed instructions regarding transmitting images to the independent radiologists, details of the HUS central reading center process, and HUS quality assurance can be found in the study MOP.

For the purposes of study endpoints assessment, head ultrasounds will be interpreted based on standard criteria of Papile et al as germinal matrix hemorrhage (IVH Grade I), or IVH Grade II, Grade III, or Grade IV based on review of standard coronal and sagittal images. IVH will be assessed in the right and left hemispheres and both results recorded, and the highest grade used as the study endpoint. Cerebellar hemorrhage will be assessed from mastoid views. Cystic periventricular leukomalacia will be assessed as radiolucent cysts in the periventricular white matter.

### **Primary Outcome measure**

#### **IVH of any grade on head ultrasound 7-10 days after birth**

Note: Infants who die prior to having a 7-10 day HUS will be considered adverse outcomes for the primary endpoint. If a surviving infant does not have a HUS performed day 7-10 this will be considered a protocol deviation, and for the purpose of the primary outcome measure, the first HUS after 10 days of age will be used.

### **Primary Adverse Event Outcome Measures**

#### ***Maternal***

- 1) Post-partum hemorrhage in the first 24 hours after delivery (≥1000 ml estimated blood loss) (y/n)
- 2) Maternal RBC transfusion (y/n)
- 3) Post-partum delivery-related infection prior to hospital discharge (y/n)
- 4) Retained placenta (y/n)

#### ***Neonatal***

- 1) NICU admission hypothermia (<36.5°C) (y/n)
- 2) Pneumothorax requiring intervention (y/n)

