## **8 ADVERSE EVENTS AND REPORTING**

Extremely preterm infants commonly have multiple clinical complications and laboratory abnormalities associated with prematurity, and those listed in section 6 will be collected and analyzed as secondary outcomes. These outcomes will be collected in the MuSIC database at times indicated in the MOP and reviewed monthly by the UVA Study Team. The DSMC will receive regular reports of secondary outcomes and compare rates in infants in the two study arms and compare overall rates in study infants to reported rates for EPT infants at NICUs in the Vermont Oxford Network or similar databases. If there is a significant imbalance of secondary outcome rates between the study arms or compared to current EPT rates, the proper course of action will be discussed by the study PIs and the DSMC.

Adverse events deemed related (definitely, probably or possibly) to a mother or infant being in the study will be collected and reported, as defined below. Recording of such adverse events will start at the time of the study intervention (birth) and will stop at the time of hospital discharge after delivery for mothers and at discharge home or 36 weeks PMA for infants. Any adverse events not resolved at the time a subject goes off study will be recorded as 'ongoing'.

Adverse events must be assessed for expectedness, severity, attribution (relatedness to the study intervention), and seriousness by the site Investigator, or another qualified study team member.

Adverse events deemed related to the intervention must be reported as SAEs if they become serious.

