### Reportable Adverse Events

The adverse events listed below may be related to the subject being in the study and are the only adverse events that will require reporting.

| Adverse Event                                                                                            | Timing                               |
|----------------------------------------------------------------------------------------------------------|--------------------------------------|
| Mother                                                                                            |                                      |
| Delivery-related infection                                                                               | Prior to discharge                   |
| Retained placenta                                                                                        |                                      |
| Other adverse events deemed by site PI to be definitely or probably related to being in the study | Any time                             |
| Infant                                                                                            |                                      |
| Hypothermia <36°C on admission to NICU                                                                   | NICU admission                       |
| Medication given for low blood pressure                                                                  | 1 st 24 hours after birth |
| Anemia: hematocrit <30% (Hgb < 10 g/dl)                                                                  | 1 st 24 hours after birth |
| Polycythemia: hematocrit >65% (Hgb > 22 g/dl)                                                            | 1 st 24 hours after birth |
| Bilirubin >12 mg/dl                                                                                      | 1 st 10 days after birth  |
| IVH grade 1-2                                                                                            | prior to 36 weeks PMA                |
|                                                                                                          |                                      |
| Cystic periventricular leukomalacia                                                                      | prior to 36 weeks PMA                |

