### Reportable Serious Adverse Events

Generally, a serious adverse event is one that is temporally associated with the subject's participation in a research study that results in death or disability, is life-threatening, or prolongs hospitalization. Many of the typical complications of prematurity fit this description and only the following SAEs possibly related to the study will be reported as such.

| Serious Adverse Event                                                                                     | Timing                                                               |
|-----------------------------------------------------------------------------------------------------------|----------------------------------------------------------------------|
| Mother                                                                                             |                                                                      |
| Any condition leading to death                                                                            | Prior to discharge                                                   |
| Post-partum hemorrhage $\geq$ 1000 mL                                                                     | In the first 24h after delivery (including delivery room blood loss) |
| Serious unexpected adverse event judged to be definitely or probably related to being in the study | Any time                                                             |
| Infant                                                                                             |                                                                      |
| Any condition leading to death                                                                            | Prior to 36 wks PMA                                                  |
| Chest compressions or epinephrine in DR                                                                   | In the delivery room                                                 |
| IVH grade 3-4                                                                                             | On 7-10 day HUS or 36 week PMA HUS                                   |
| Cerebellar hemorrhage                                                                                     | On 7-10 day HUS or 36 week PMA HUS                                   |

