| Pneumothorax requiring intervention                                                                       | 1 st 24 hours after birth                                 |
| Exchange transfusion for hyperbilirubinemia                                                               | 1 st 10 days after birth                                  |
| Serious unexpected adverse event judged to be definitely or probably related to being in the study | Any time                                                             |

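### Three of the six primary adverse event outcomes do not match the protocol's reporting tables or data-collection list, so adverse event reports can show lower rates than the outcomes for the same named harm

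*Protocol*

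**What the plan says.** Protocol Section 6, Primary Adverse Event Outcome Measures, lists four maternal and two neonatal outcomes. The two neonatal ones are "NICU admission hypothermia (<36.5°C) (y/n" and "Pneumothorax requiring intervention (y/n". One of the four maternal ones is "Maternal RBC transfusion (y/n".

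Section 8 then sets out what sites report.

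- Its table of adverse events contains "Hypothermia <36°C on admission to NICU", and the text above that table says that the listed events "are the only adverse events that will require reporting".
- Its table of serious adverse events contains "Pneumothorax requiring intervention", with the first 24 hours after birth in the timing column. The text above that table says that "only the following SAEs possibly related to the study will be reported as such".
- Maternal transfusion is in neither table.
- Each table has catch-all rows for mother and infant. They cover other events that the site judges definitely or probably related to study participation; in the serious table the event must also be serious and unexpected.

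Section 4, Prohibited and Concomitant Medications, limits the medication and blood-product data to the items listed there. The maternal list has prenatal steroids, magnesium and oxytocin. The only red cell item is the infant's transfusions to day 10.

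**The concern.** These outcomes are harms that the intervention could plausibly change: the infant reaches the resuscitation table later, mask pressure is given before clamping, and the mother's cord is clamped later. For a harm that the protocol ranks as primary, a reader should find one definition, one window and a clear route of collection.

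For half of the list this is not so. Section 7 tabulates adverse events by arm and cohort, and sends the Data and Safety Monitoring Committee periodic reports of adverse and serious adverse events. Section 6, Safety, compares outcomes and reportable events between arms side by side. The committee could then see two rates under one event name, with nothing in the protocol to say which is the primary harm. For maternal transfusion, the protocol names a primary harm that its own collection list leaves out.

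**Working it through.** The protocol states no figure to reproduce here. The check sets the definitions side by side.

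| Primary adverse event outcome (Section 6) | Section 6 definition | Section 8 reporting entry | Agree? |
|---|---|---|---|
| Post-partum hemorrhage | at least 1000 ml, first 24 h | serious event: at least 1000 ml, first 24 h | yes |
| Maternal red cell transfusion | yes/no | none | no entry |
| Delivery-related infection | before discharge | adverse event: before discharge | yes |
| Retained placenta | yes/no | adverse event | yes |
| Hypothermia at NICU admission | below 36.5°C | adverse event: below 36°C | threshold differs |
| Pneumothorax needing intervention | no window stated | serious event: first 24 h | window differs |

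Three of six do not agree: both neonatal outcomes and one of the four maternal ones.

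**Hypothermia.** Let T be the admission temperature. Every infant with T < 36.0 also has T < 36.5, so the listed adverse event is a subset of the outcome. Infants with 36.0 ≤ T < 36.5 have the outcome and no listed report. The share of outcome events without a listed report is 1 − P(T < 36.0) / P(T < 36.5). This cannot be negative, so the listed row cannot give a higher rate than the outcome.

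The documents give no temperature distribution, so the share is unknown. Purely as an assumption, take T as normal with mean 36.3 to 36.9°C and SD 0.5 to 0.9°C:

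- mean 36.3, SD 0.9: 1 − 0.369/0.588 = 0.37
- mean 36.6, SD 0.7: 1 − 0.196/0.443 = 0.56
- mean 36.9, SD 0.5: 1 − 0.036/0.212 = 0.83

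A range of 37% to 83% under invented inputs shows only that the half-degree could matter. It does not estimate what this trial will see.

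**Pneumothorax.** Section 6 gives no time limit. Two maternal outcomes in the same list (hemorrhage and infection) do carry one, so reading the silence as no limit within follow-up is fair, but it is an inference. On that reading, an infant treated on day 2 has the outcome and no listed serious event.

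**Maternal transfusion.** A transfused mother with blood loss below 1000 ml, and no other listed event, has a primary adverse event outcome and no listed report. The item is also absent from the Section 4 medication and blood-product list, and from the maternal chart items in Section 4 under the post-delivery instructions for the OB team (hemorrhage, retained placenta, infection).

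**The case against.** The strongest reply is that outcomes and event reports are two separate streams, and only the second is narrow. Much of this stands.

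- The opening of Section 6 says that, apart from the outside head ultrasound readings, outcome measures are found in the medical record.
- The opening of Section 8 says of the infants' complications that "those listed in section 6 will be collected and analyzed as secondary outcomes", and it gives the committee regular reports of those outcomes.
- Section 6, Tertiary Outcome Measures, records admission temperature itself, so every infant below 36.5°C can be identified.
- Section 4 has maternal data taken from the chart until discharge, and Section 7 refers to secondary endpoints for mothers.

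A reader might infer that the primary harms themselves will be under-counted, or that a pneumothorax after 24 hours will not be captured at all. The documents do not support either: the shortfall is confined to adverse event and serious adverse event reporting, and even there the catch-all rows may pick up some events.

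The reply also holds that a reporting trigger may be narrower than an outcome, as with hematocrit and bilirubin, which are outcomes in Section 6 and reportable only beyond a cut-off in Section 8. That comparison is weaker. Those outcomes are recorded as values, so a report needs some cut-off. Hypothermia is a yes/no outcome given two different cut-offs. The protocol nowhere says that the two lists are meant to differ. The Expectedness subsection of Section 8 points to Section 6 for its adverse events, and the other three primary adverse event outcomes match.

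The catch-all rows do not close the gap. They depend on a site's judgement of relatedness in a trial whose intervention cannot be blinded.

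Separate collection does not fully answer the transfusion point either. The Section 8 sentence concerns the infants' complications of prematurity, and the Section 4 list that limits blood-product data omits the mother.

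**Conclusion.** The inconsistency stands for three of the six primary adverse event outcomes: a different threshold for hypothermia, a different window for pneumothorax (reading the silence in Section 6 as no limit), and no reporting entry and no place on the collection list for maternal transfusion. Tabulations and committee reports built from adverse event and serious adverse event forms can give lower rates than the Section 6 outcomes. The direction follows from the definitions; the size cannot be estimated from the documents.

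It would go too far to attach a count of missed infants, or to claim a biased arm comparison: neither is shown. The statistical safety bounds in Section 7 concern high-grade IVH only, and the primary endpoint, sample size and interim analysis are untouched. The point is still worth correcting, because it leaves two possible rates for one named harm and one primary harm without a stated route of collection.

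**What to change.** 1. Reconcile Section 6, Primary Adverse Event Outcome Measures, with the two reporting tables in Section 8, so that each of the six outcomes has one threshold and one time window. Both are for the sponsor to choose. If a reporting trigger is meant to differ from the outcome, say so and give the reason.
2. Add maternal red cell transfusion to the data collected in Section 4.
3. State that the arm comparison and the committee's tables for these six outcomes use the Section 6 definitions, taken from the collected data (admission temperature, pneumothorax with its date, maternal transfusion) and not from adverse event or serious adverse event forms.

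The cost is protocol wording and minor extra data entry and reporting. Admission temperature is already recorded, and the other two items can be taken from medical records that the coordinators already review. The intervention, sample size and primary analysis do not change.

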### **Secondary Outcome Measures**

#### ***Neonatal***

- 1) **Delivery Room**

- Apgar scores <5 at 5 minutes (y/n)
- 2) First 24 hours after birth:**
  - Lowest hematocrit (median, min, max, 25th & 75th percentiles)
  - Medication for low blood pressure (e.g., hydrocortisone or vasopressors) (y/n)
- 3) First 10 days after birth**
  - Number of RBC transfusions since birth (median, min, max, 25th & 75th percentiles)
- 4) Hospital course until 36 weeks' PMA**
  - Composite severe brain injury (y/n) based on local radiologist's read of the early or late HUS and defined as the presence of:
    - Grade 3-4 IVH or
    - Cerebellar hemorrhage or
    - Cystic periventricular leukomalacia (cPVL)
  - Death prior to 36 weeks PMA (y/n)

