Of note, infants randomized to the “Standard” group will be getting 30-60 seconds of DCC, which is within the range of previous clinical trials and is the current recommendation from ACOG. It is not known whether 120 sec of DCC is more beneficial than 30-60 sec. This would not be feasible to study for this population, since most practitioners would not accept delaying resuscitation of non-breathing EPT infants for 120 seconds during DCC.

The study intervention cannot be blinded but the primary outcome will be assigned by expert radiologists at non-study institutions who will be blinded to study arm.

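### The secondary outcome of severe brain injury is defined on local scan reads, which the same section of the protocol bars from secondary outcomes in favour of a blinded central read

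*Protocol*

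**What the plan says.** Section 6 of the Protocol, under Specification of the Appropriate Outcome Measures, sets up two streams of head ultrasound (HUS) reading.

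- **Local.** For care and adverse event reporting, "all HUS's will be read per standard of care by board-certified pediatric radiologists trained in neonatal HUS interpretation at each study site". Of these local reports it then says: "These reports will not be used for primary or secondary study outcomes assessment".
- **Central.** For study endpoints, an outside radiologist blinded to assignment "will independently read the 7-10 day and the final 36 week PMA HUS on each study infant".

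The opening of Section 6 agrees. It describes outcome measures as routine-care data, "with the exception of outside expert readings of HUS at 7-10 days and last HUS at birth hospital prior to 36 weeks". The late scan also has a stated purpose: it "will be used for the secondary HUS outcome assessment".

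The Secondary Outcome Measures list, under the hospital course to 36 weeks, then gives: "Composite severe brain injury (y/n) based on local radiologist's read of the early or late HUS". The components are grade 3-4 IVH, cerebellar hemorrhage and cystic periventricular leukomalacia (cPVL).

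**The concern.** The two statements name different readers for the same outcome, so the data source of a named secondary outcome is not fixed. The choice could then be made after both sets of reads are available.

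The reader matters because the delivery-room intervention is open. The Rationale for Study Design gives outside reading as the answer to that: "The study intervention cannot be blinded but the primary outcome will be assigned by expert radiologists at non-study institutions". That sentence concerns the primary outcome, but Section 6 extends blinded reading to study endpoints generally. Local radiologists work at the site that delivered the intervention and are nowhere said to be blinded. A composite built on their reads would lack the protection that the rest of the section plans for it. The trial report could also show one grade for a scan in the primary analysis and another in the composite.

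**Working it through.** The point turns on wording and no stated figure depends on it, so the check sets the texts side by side.

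1. **Is there a real conflict?** The general text excludes local reports from primary and secondary outcomes. The composite is on the secondary list and is defined by the local report. Both are current text, and no other section reconciles them.

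2. **Could the exclusion be aimed at other secondary outcomes?** The list has six entries: low 5-minute Apgar score, lowest hematocrit, medication for low blood pressure, number of red cell transfusions, the brain injury composite, and death before 36 weeks. Only the composite uses imaging. If it is exempt, the exclusion of local reports from secondary outcomes applies to nothing, and the central read of the late scan serves no listed secondary outcome, although the late scan is assigned to that use.

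3. **Is the central read equipped to supply the composite?** Section 6 sets out, for endpoint reading, how to grade IVH, how to assess cerebellar hemorrhage (from mastoid views) and how to recognise cPVL. Those are the three components. For infants with the two planned scans, no further reading is needed.

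4. **Would the discrepancy rule reconcile the two reads?** A second independent radiologist is called only when local and central findings differ in a way that would change the primary outcome, which is IVH of any grade, with death before the scan counted as an adverse outcome.

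| Local and central reads differ on | Changes primary? | Can change composite? | Second independent read? |
|---|---|---|---|
| No IVH vs grade 1 | Yes | No | Yes |
| Grade 2 vs grade 3 | No | Yes | No |
| Cerebellar hemorrhage only | No | Yes | No |
| cPVL only | No | Yes | No |

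   The last three rows are typical of the disagreements that decide the composite, and none has a stated resolution.

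5. **Where does the central read not reach?** There are two groups. Where a center does brain MRI in place of the late HUS, Section 6 accepts the MRI for secondary outcomes but names no central reader for it. An infant who dies before the 7-10 day scan may have only an earlier scan, read locally. In addition, the list does not define early and late HUS. The 7-10 day and final scans are the natural reading, but several routine scans are done in each infant.

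**The case against.** The definition in the outcome list is the more specific text and names the local read outright, so it may be a deliberate exception. A local read covers every scan and every infant, including those with late MRI or early death, whom the planned central read misses. The readers are board-certified pediatric radiologists doing routine work, and the intervention lasted two minutes in the delivery room, so they may well not know the arm. A statistical analysis plan, not available here, may settle the matter.

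Part of this stands. Coverage is a real advantage of local reads, and a simple switch to central reads would leave some infants without a stated reader. A deliberate exception is also possible, but the Protocol neither states nor justifies one, and step 2 of the working shows that it would empty the general rule. An analysis plan could follow only one of the two statements and would contradict the other.

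A reader might infer that the severe brain injury result will be biased. The documents do not support that: they say neither that local readers know the arm nor that they are blinded. Nor can the size of any bias be estimated. The Protocol gives no rate for the composite and no figure for disagreement between readers. The 9.6% mean rate under Guidelines for Safety Monitoring is for high-grade IVH alone.

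**Conclusion.** The contradiction is real and should be fixed before the composite is analysed. It affects one of six secondary outcomes. The primary outcome rests on central review throughout, and the sample size, power, alpha and interim bounds do not use the composite, so a reader should not take this as a flaw in the trial's main comparison.

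What is lost if local reads are used is a planned protection against detection bias in an open trial. Whether bias would follow is unknown. This conclusion assumes that early and late HUS mean the 7-10 day and final scans, and that no document outside the Protocol already reconciles the two statements.

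**What to change.** In the Secondary Outcome Measures list:

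- Define the composite and its three components on the blinded central read of the 7-10 day and final HUS, and name those two scans in place of early and late.
- Use the local read for a sensitivity analysis. It keeps its role in care and adverse event reporting.
- For infants with late MRI in place of HUS, or with no centrally read scan (for example, death before the 7-10 day scan), state that the local report is used and flagged, and report how many by arm.
- State which read counts when central and local reads differ on a component that does not change the primary outcome.

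If local reads are in fact intended, amend the general text on reading in Section 6 instead, so that it states the exception for this composite and gives the reason.

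The cost is a short text amendment, somewhat more than one line because of the MRI, missing-scan and disagreement rules. The central HUS reads are already planned, and the flagged local fallback avoids adding a reader. Sample size and the primary analysis do not change.
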